**d.8. Sample size**:

***Effect of RDT+ACT on in the incidence of malaria***: To assess the effect of RDT+ACT on the incidence of malaria children under 48 months of age would require 30 clusters (15 per arm) and 200 PYAR per cluster on the basis of the following assumptions: (1) Incidence of malaria in the clinical judgement + ACT group would be 0.8 episode/ 1 PYAR (the rate observed in the IPTi group of <24 month old children in Navrongo, Ghana6); (2) The study would have 80% power at 95% significance level to detect a 20% difference in the incidence of malaria between the two comparison groups and this level of difference is deemed to be the non-inferiority margin of public health importance; (3) the coefficient of variation in the incidence of malaria between clusters will be 0.18

***Effect of RDT+ACT on in the incidence of severe anaemia***: Incidence of severe anaemia in the RDT + ACT group is expected to be 37/1000 PYAR (the rate observed in the 16-24 month old children who received placebo in Navrongo, Ghana6). The study would have 80% power at 95% significance level to detect a 36% reduction in the incidence of severe anaemia between the two comparison groups.

***Effect of RDT + ACT on febril children requiring referral:*** Actively following up 2000 episodes of febrile illness seen at 20 study HCs will have 85% power to detect 50% difference between the two arms assuming 1) risk of referral in the RDT + ACT group would 0.05; (2) the coefficient of variation in the risk of referral 0.1

Although mortality will be measured the study does not have adequate power to detect any difference between the groups.

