***Primary:***

What is the effect of restricting ACT to RDT positive cases of malaria compared to offering ACT on the basis of clinical judgement on the incidence of malaria in children < 4 years of age?

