**e.4.Study site and population**

The study will link to Stage 2 – component A – “effects of restricted use of ACTs based on RDT results: a randomised controlled trial”**.** Outcomes will be measure in this RCT and costs will be measured in 7 out of the 28 health centres involved in the trial.The health centres involved in the costing exercise will be selected using simple random sampling from those selected for the trial.

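### One undirected 20% serves as both the difference to detect and the non-inferiority margin; at two-sided 5%, 15 clusters per arm give 69% to 77% power against a rise or margin, depending on the criterion

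*Protocol*

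**What the plan says.** The primary question (Protocol d.1, Primary) is open: "What is the effect of restricting ACT to RDT positive cases of malaria compared to offering ACT on the basis of clinical judgement". It names no non-inferiority hypothesis, and neither does the primary outcome in d.3.

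The sample size paragraph (Protocol d.8) says the trial "would require 30 clusters (15 per arm) and 200 PYAR per cluster". Its assumptions are:

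- "Incidence of malaria in the clinical judgement + ACT group would be 0.8 episode/ 1 PYAR"
- "80% power at 95% significance level to detect a 20% difference in the incidence of malaria between the two comparison groups"
- "the coefficient of variation in the incidence of malaria between clusters will be 0.18"

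The second assumption continues that "this level of difference is deemed to be the non-inferiority margin of public health importance". The paragraph does not say whether the 20% is a rise or a fall, whether the margin is a rate difference or a rate ratio, or whether the test is one- or two-sided.

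The costing component (Protocol e.4) says "costs will be measured in 7 out of the 28 health centres involved in the trial", against 30 in d.8.

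**The concern.** Detecting a 20% difference and excluding a 20% margin are separate objectives. The first assumes that the arms truly differ by 20% and asks whether the null of equality is rejected. The second usually assumes that the arms are about equal and asks whether a difference as large as the margin can be ruled out. Variances, power and conclusions all differ.

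Direction matters too. The RDT+ACT arm limits ACT to test-positive children, so a non-inferiority margin has to cap an increase in malaria: from 0.80 to 0.96 per PYAR if the 20% is taken on the clinical-judgement rate. With a constant coefficient of variation, a higher rate brings a larger between-cluster variance, so a rise is harder to detect than a fall of the same size.

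Two things are at stake. Readers will rely on 80% power for an objective to which it may not apply. And with no decision rule tied to the margin, nothing in the text prevents a non-significant difference from being taken as evidence that restricting ACT is no worse.

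**Working it through.** **Inputs from the protocol.** Control rate r0 = 0.8 per PYAR, y = 200 PYAR per cluster, k = 0.18, 20% of r0 = 0.16, 80% power (all d.8). The 200 PYAR equals 100 children × 2 years (d.4), so nothing is allowed for loss to follow-up.

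**Assumptions added here.** Two-sided 5%, equivalent to one-sided 2.5%, so (1.960 + 0.842)² = 7.849; and the usual +1 cluster per arm.

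**Formulas.** On the difference scale (Hayes–Bennett):

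c = 1 + 7.849 × V/d², with V = (r0 + r1)/y + k²(r0² + r1²)

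Power at c per arm = Φ(√[(c − 1) d²/V] − 1.96)

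On the log-ratio scale with equal rates, V = 2 × (k² + 1/(r0 y)) and d = ln 1.20.

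**The plan's own figure first (20% fall, r1 = 0.64).** V = 1.44/200 + 0.0324 × 1.0496 = 0.04121. V/d² = 0.04121/0.0256 = 1.610. c = 1 + 7.849 × 1.610 = 13.63, so 14 per arm. The stated 15 is one per arm above this.

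**The other readings.**

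- 20% rise, r1 = 0.96: V = 1.76/200 + 0.0324 × 1.5616 = 0.05940; V/d² = 2.320.
- Non-inferiority, equal rates, absolute margin 0.16: V = 1.60/200 + 0.0324 × 1.28 = 0.04947; V/d² = 1.933.
- Non-inferiority, equal rates, rate ratio 1.20: V = 2 × (0.0324 + 0.00625) = 0.0773; d² = 0.03324; V/d² = 2.325.

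| Reading | Clusters per arm for 80% | Power at 15 per arm | Power at 14 per arm |
|---|---|---|---|
| Detect a 20% fall | 13.63, so 14 | 83.9% | 81.1% |
| Detect a 20% rise | 19.21, so 20 | 69.0% | 65.8% |
| Non-inferiority, margin 0.16 per PYAR | 16.17, so 17 | 76.8% | 73.7% |
| Non-inferiority, rate ratio 1.20 | 19.25, so 20 | 68.9% | 65.7% |

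A noncentral t calculation at 15 per arm agrees to within about 0.1 percentage points.

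**Conventions that bring 15 per arm to about 80% or above.**

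- One-sided 5% (1.645 in place of 1.96): 79.1% for the rise, 85.2% for the absolute margin, 79.1% for the ratio margin.
- One-sided 2.5% with the absolute margin and no +1 term: c = 7.849 × 1.933 = 15.17; power at 15 is 79.6%.
- The 20% taken on the RDT+ACT rate, so that 0.8 is compared with 1.0 (a 25% rise on control): c = 13.19; power at 15 is 85.1%.

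**Loss to follow-up.** At 180 PYAR per cluster, power at 15 per arm is 68.3% for the rise and 76.0% for the absolute margin, so this matters little beside the choice of hypothesis.

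**The case against.** The strongest reply is that the shortfall rests on conventions which the protocol does not state. Its 95% significance level carries no sidedness, and non-inferiority is inherently a one-sided question. At one-sided 5%, or with the absolute margin and no +1 term, 15 per arm gives 79% to 85%. On that view d.8 is under-specified, and no arithmetic error has been shown. This stands, and it limits the point: the figures below 80% are conditional. It does not rescue the text, because power runs from 69% to 85% over choices that d.8 leaves open, so the stated 80% cannot be tied to the non-inferiority objective.

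A reader might infer that the trial was sized for a fall in malaria, especially since 28 centres in e.4 equals the 14 per arm of that calculation. The documents do not support this. The fall reading does not return the stated 15, and some rise or margin readings come closer to 15 per arm with 80% power. The match with 28 may be coincidence.

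A reader might also infer that the investigators intend to declare non-inferiority from a non-significant test. The protocol states no such rule, and the analysis plan is not shown. The risk comes from the missing decision rule; no intention is stated.

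Detailed analysis rules may properly be left to an analysis plan. Here, though, the protocol itself fixes a margin and a power figure, and those two have to agree.

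**Conclusion.** The point holds as a badly fixed primary hypothesis with a power figure that does not clearly belong to it. Section d.8 attaches one undirected 20% to two different objectives, and d.1 names neither.

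Assuming two-sided 5% (one-sided 2.5%), the +1 term, 200 PYAR per cluster, k = 0.18 and the 20% taken on the clinical-judgement rate, 15 per arm delivers the stated power for a fall (84%). In the direction that a margin must protect it does not: 69% to detect a 20% rise, 77% for non-inferiority on the absolute scale, 69% on the ratio scale. These answer different questions and should not be merged into one range. Eighty per cent would need 17 to 20 clusters per arm, depending on the criterion.

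The 30 and 28 health centres contradict each other whatever formula is used. If 28 is right, the same four figures are 81%, 66%, 74% and 66%.

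**What to change.** 1. In d.1 and d.8, state that the primary hypothesis is non-inferiority of RDT+ACT. Express the margin as a rise in malaria incidence under RDT+ACT, and give its scale (rate difference or rate ratio), the rate on which the 20% is taken, and the one-sided alpha.
2. State that non-inferiority is judged by the upper confidence limit from a cluster-level analysis, and that a non-significant difference does not show non-inferiority.
3. Restate the power for the criterion chosen. For example, with an upper limit of the two-sided 95% interval for the rate ratio below 1.20, power is about 69% at 15 per arm and 66% at 14. With an absolute margin of 0.16 per PYAR it is about 77% and 74%. Both assume equal true rates.
4. Reconcile the 30 health centres of d.8 with the 28 of e.4 and use one number throughout.

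The cost is a few sentences and, under the conventional alpha, a less favourable stated power. Recovering 80% by adding clusters is constrained: 17 per arm is 34 centres and 20 per arm is 40, while d.2 counts 36 government facilities in the area.

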**d.7. Measuring outcomes**:

***Incidence of malaria:***

Passive surveillance: All study children presenting with a history of fever to the study HCs will be identified using photoID cards and assessed with a morbidity questionnaire and a blood sample (blood slide and filter paper) will be collected to assess malaria parasite. Since the decision to offer an antimalarial drug will be based on RDT results or clinical judgment the blood slides will have limited use for treatment decision making. However, the blood slides will be at Kintampo Health Research Centre and the results will be reported to the health centres.

Active surveillance: Study children will be visited once a month at home and a morbidity questionnaire and blood samples (blood slide and filter paper) will be collected to assess malaria parasite if a child has a history of fever in the past 48 hours. Those who have a positive blood slide will be treated with ACT.

Both passive and active surveillance of malaria will be continued for 24 months from enrolment.

***Incidence of severe anaemia***:. All study children attending study HCs will be clinically assessed using a morbidity questionnaire and the Hb will be tested using a haemacue machine if anaemia is suspected by clinical examination. Children with Hb <11 gms/dl will be given appropriate treatment according to the national treatment protocol.

***Incidence of severe febrile illness and mean number of sick days:*** These outcomes will be measured in 100 episodes of febrile illness (50 in the wet and 50 in the dry season) in 10 randomly selected study HCs per arm. These children will be actively followed up on day 1,2,3 and 7 post treatment to assess the progress of their illness. If the illness has resolved by day 7, the number days the child was ill will be collected from the caretaker’s report. If the illness has not resolve by day 7 the child will be referred to the hospital and the number of days of illness will be collected from hospital discharge summary. The mean number of days of illness and the proportion of children requiring reference will be compared between the two groups.

***Use of antibiotics:*** The use of antibiotics will be monitored through the morbidity questionnaire completed during each visit to the study PHCs by study children.

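### The stated 85% power for referral is about 78% under a two-sided 5% test; d.8 should also state alpha, sidedness, direction and the severe-anaemia coefficient of variation

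*Protocol*

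**What the plan says.** Protocol section d.8 (Sample size) gives a separate power statement for febrile children requiring referral. It says that the 2000 actively followed episodes "seen at 20 study HCs will have 85% power to detect 50% difference between the two arms". It lists two assumptions: "risk of referral in the RDT + ACT group would 0.05" and "the coefficient of variation in the risk of referral 0.1". It gives no significance level for this outcome, does not say whether the test is one- or two-sided, and does not say whether the other arm is expected to be lower or higher.

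Section d.7 (Measuring outcomes) supplies the layout. The HCs are chosen "in 10 randomly selected study HCs per arm", and the same paragraph gives the number of episodes: "These outcomes will be measured in 100 episodes of febrile illness (50 in the wet and 50 in the dry season"). Since 2000 / 20 = 100, this means 100 episodes in each of 20 HCs, 10 per arm.

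For severe anaemia, d.8 takes 37/1000 PYAR in the RDT + ACT group and claims 80% power at the 95% level to "detect a 36% reduction in the incidence of severe anaemia between the two comparison groups". It gives no CV for this outcome. The only CVs in the section are 0.18 for malaria incidence and 0.1 for referral.

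**The concern.** The referral statement prints almost every input that a cluster-trial power calculation needs, so it can be checked. On the usual two-sided reading the inputs do not give 85%. The severe-anaemia statement cannot be checked in the same way, because its CV is missing.

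Both outcomes are secondary, but they bear on whether withholding ACT from RDT-negative children does harm, and d.8 itself says that mortality is underpowered. If the planned power is overstated, a null result on referral looks more reassuring than it should.

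**Working it through.** **Referral: inputs**
- Clusters per arm, c = 10 (d.7)
- Episodes per cluster, m = 100 (d.7; 2000 / 20 from d.8)
- Risk in RDT + ACT arm, p0 = 0.05 (d.8)
- Other arm, p1 = 0.025 (a halving; direction not stated)
- CV, k = 0.1 (d.8)
- Test: two-sided 5% (assumption; d.8 states neither alpha nor sidedness for this outcome)

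**Formula** (Hayes-Bennett, unmatched clusters)

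V = [p0(1 − p0) + p1(1 − p1)]/m + k²(p0² + p1²)

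power = Φ( √[(c − 1)(p0 − p1)²/V] − z )

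**Numbers**

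V = (0.0475 + 0.024375)/100 + 0.01 × (0.0025 + 0.000625) = 0.00071875 + 0.00003125 = 0.00075

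√(9 × 0.000625/0.00075) = √7.5 = 2.739; 2.739 − 1.960 = 0.779; power = **78.2%**

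A noncentral-t calculation gives 77.9%, and a simulation with a cluster-level t-test gives 78.5%.

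**Attempts to reproduce the 85% (0.05 against 0.025)**

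| Variant | Power |
| --- | --- |
| Two-sided, k = 0.1, c − 1 | 78.2% |
| Two-sided, k = 0.1, c in place of c − 1 | 82.3% |
| Two-sided, design-effect method | 81.9 to 82.4% |
| Two-sided, k = 0, c − 1 | 79.9% |
| Two-sided, k = 0, c in place of c − 1 | 83.9% |
| One-sided 5%, k = 0.1, c − 1 (2.739 − 1.645 = 1.094) | 86.3% |

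No two-sided version of this contrast reaches 85%. The one-sided version does.

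**Other readings of a 50% difference** (two-sided, k = 0.1, c − 1): 0.05 against 0.075 gives 56.4%; 0.05 against 0.10, where 0.05 is the already halved risk, gives 97.2%. Neither matches 85%. They show why the direction must be stated.

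**Severe anaemia** (15 clusters per arm and 200 PYAR each, taken from the malaria calculation in d.8; two-sided 5%)

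r0 = 0.037; r1 = 0.64 × 0.037 = 0.02368; difference = 0.01332

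V = (r0 + r1)/200 + k²(r0² + r1²) = 0.0003034 + k² × 0.00193

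| k | Power with c − 1 | Power with c |
| --- | --- | --- |
| 0 | 81.6% | 84.2% |
| 0.10 | 79.2% | 81.9% |
| 0.18 | 74.1% | 76.9% |

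Exactly 80% corresponds to k of about 0.08 with the correction, or about 0.136 without it.

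**The case against.** **Sidedness.** The strongest defence is that the protocol never says the test is two-sided. With every stated input and a one-sided 5% test, referral power is 86.3%, which agrees with 85%. One-sidedness is not far-fetched: d.8 speaks of a non-inferiority margin for malaria, and 0.8 against 0.96 with 15 clusters per arm gives 79.1% one-sided. So a reader might infer that 85% is wrong outright, but the documents support only the conditional statement. Two things still favour a two-sided test for referral. The text speaks of a difference between arms without naming a direction. The 80% for anaemia also lies near the two-sided values at small CVs (81.6% at 0, 79.2% at 0.1), whereas one-sided values at the same CVs are 88.8% and 87.1%.

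**Small-cluster correction.** The c − 1 term is a choice of formula and accounts for about 4 points (82.3% against 78.2%). This stands, and is why the range is given. Even without it the figure is below 85%.

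**Was clustering ignored?** A reader might infer this, because the unclustered figure (about 84%) lies close to 85%. It is not established: a CV of 0.1 costs under 2 points (83.9% to 82.3%, or 79.9% to 78.2%), so the gap does not identify the cause.

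**Severe anaemia.** A reader might infer that the 80% is really 74%. The documents do not support that. The 0.18 is given for malaria only, no CV is given for anaemia, and 80% is reproduced closely at 0.1. Nor does it show an error that the planning rate is "the rate observed in the 16-24 month old children who received placebo in Navrongo". The source is disclosed. Turning the age band into a power loss needs an assumed spread of entry ages and an assumed lower rate, and the protocol gives neither.

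**Impact.** Both outcomes are secondary, and the 30 clusters are derived from malaria. In terms of detectable effect the shift is small: on the two-sided corrected formula, 80% power corresponds to a 51% difference and 85% power to a 54% difference, against the 50% stated. A null result would also be judged mainly by its confidence interval. This limits the weight of the point but does not make the printed figure correct.

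**Conclusion.** The point holds for referral, on the condition that the test is two-sided at 5% and the contrast is 0.05 against 0.025. Power is then about 78% (82% without the small-cluster correction), 3 to 7 points below the stated 85%. The chance of missing a true halving is about 18 to 22%, not 15%. If a one-sided 5% test was intended, 85% is about right, but the protocol would have to say so.

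For severe anaemia the defect is an omission: the 80% cannot be verified without a CV. It is neither confirmed nor refuted.

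**What to change.** In d.8:
- Give referral power as about 78%, with its conditions beside it: two-sided 5%, 0.05 against 0.025, CV 0.1, 10 HCs per arm and 100 episodes each. If a one-sided test was meant, state and justify that instead.
- State alpha, sidedness and the direction of the 50% difference for referral.
- State the between-cluster CV behind the 80% for severe anaemia. It would help to show the sensitivity: about 79% at 0.1, and about 74% if the malaria value of 0.18 applied. Do not replace the 80% with 74%.

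The cost is a few lines of text and one less favourable figure, with no change to conduct. If the sponsor prefers to keep 85% with a two-sided test, the same formula gives about 12 HCs per arm at 100 episodes: 1 + (1.960 + 1.036)² × 0.00075/0.000625 = 11.8. The alternative is about 121 episodes per HC at 10 HCs per arm. Either would add to the active follow-up.

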**d..9 Effect of other malaria control interventions**

Coverage with other malaria control interventions, such as insecticide treated nets (ITNs) will be assessed during the prevalence surveys. Conclusions on the efficacy of the alternative case management strategies will be generalisable at the coverage levels of other interventions present in the study area. Antimalarial and other drugs are available in several formal and informal sector outlets and this may affect the adherence to the treatment regime of the study participants. Attempts will be made to maximise adherence to study protocol by participants through behaviour change communication strategies. At the monthly active follow up visits of study children the history of treatment received from any other health care provider other than the designated HCs will be documented and this information will be used to assess the extent of contamination of the study outcomes.

**d.10 Summary of data and biological sample collection per child**

| Procedures | enrolment | Unscheduled visits to PHCs | Monthly Scheduled home visits |
| --- | --- | --- | --- |
| Consent | √ |  |  |
| PhotoID | √ |  |  |
| Baseline socio-demographic, contextual factors CRF | √ |  |  |
| RDT testing |  | √ |  |
| ACT based on RDT result |  | √ (only In RDT+ACT PHCs) |  |
| Morbidity CRF |  | √ | √ (if history of fever in past 2 days) |
| Blood slide and filter paper sample |  | √ | √ (if history of fever in past 2 days) |
| Hb (Haemacue) |  | √ | √ (if history of fever in past 2 days) |

**d.11. Ethical issues**

Children in both arm of the study will be given standard care currently available in Ghana and all children will be closely monitored for any unexpected events. An informed written consent will be obtained from caretakers of the study children prior to enrolment. Ethical approval from the LSHTM and Kintampo Health Research Centre ethics committee will be obtained before starting the trial. The decision to progress to stage 2 of the study will be made by the Data Safety Monitoring Board.

**e. Stage 2 – component B: Cost effectiveness analysis**

**e.1.Research question**

**Primary**

What is the cost effectiveness of RDT based ACT for treatment of children under 4 years compared with ACT based on clinical judgement?

**Secondary**

What are the costs of alternative treatments where ACT is based on RDT results compared to ACT based on clinical judgement?

What are the cost implications for a District Health Management Team (DHMT) of making RDT based ACT policy?

What are the implications of the health insurance scheme for the cost effectiveness and equity of RDT based ACT?

**e.2. Study perspective**

The societal perspective will be taken and therefore will include costs to all those involved in the project including the children with fever and their carers. The provider perspective will be taken in assessing the cost implications for a DHMT of introducing RDTs into their health centres.

**e.3. Primary costs and outcomes**

**Costs**

Cost of treatment of febrile children with ACT based on positive RDT tests

Cost of treatment of febrile children with ACT based on clinical judgement

**Outcomes**

Incidence of malaria in children under 48 months of age

Incidence of sever anaemia in children under 48 months of age

Incidence of severe febrile illness in <48 month old children

**Secondary costs and outcomes**

**Costs**

Cost of treatment of febrile children under 48 months (ACTs + antibiotics + other treatments) in those tested with an RDT

Cost of treatment of febrile children under 48 months (ACTs + antibiotics + other treatments) based on clinical judgement alone

